## Abstract

**Background:**

Women with breast cancer undergoing chemotherapy suffer from a number of symptoms and report receiving inadequate support from health care professionals. Innovative and easily accessible interventions are lacking. Breast Cancer e-Support is a mobile Application program (App) that provides patients with individually tailored information and a support group of peers and health care professionals. Breast Cancer e-Support aims to promote women’s self-efficacy, social support and symptom management, thus improving their quality of life and psychological well-being.

**Methods:**

A single-blinded, multi-centre, randomised, 6-month, parallel-group superiority design will be used. Based on Bandura’s self-efficacy theory and the social exchange theory, Breast Cancer e-Support has four modules: 1) a Learning forum; 2) a Discussion forum; 3) an Ask-the-Expert forum; and 4) a Personal Stories forum. Women with breast cancer (*n* = 108) who are commencing chemotherapy will be recruited from two university-affiliated hospitals in China. They will be randomly assigned to either control group that receives routine care or intervention group that receives routine care plus access to Breast Cancer e-Support program during their four cycles of chemotherapy. Self-efficacy, social support, symptom distress, quality of life, and anxiety and depression will be measured at baseline, then one week and 12 weeks post-intervention.

**Discussion:**

This is the first study of its kind in China to evaluate the use of a mobile application intervention with a rigorous research design and theoretical framework. This study will contribute to evidence regarding the effectiveness of a theory-based mobile application to support women with breast cancer undergoing chemotherapy. The results should provide a better understanding of the role of self-efficacy and social support in reducing symptom distress and of the credibility of using a theoretical framework to develop internet-based interventions. The results will provide evidence to support the implementation of an innovative and easily accessible intervention that enhances health outcomes.

**Trial registration:**

ACTRN: ACTRN12616000639426, Registered 17 May, 2016.

**Electronic supplementary material:**

The online version of this article (doi:10.1186/s12885-017-3276-7) contains supplementary material, which is available to authorized users.

## Background

Breast cancer is a major global public health problem. In China, breast cancer is growing as the most common cancer and the 6th leading cause of cancer-related death among women [1]. Adjuvant chemotherapy is a common treatment for invasive breast cancer in China, with approximately 81.4% of these women receiving chemotherapy [2]. The physical and psychological symptoms that occur after diagnosis and during chemotherapy can have a negative impact on the women’s quality of life (QoL) and psychological well-being [3]. Symptom management is therefore beneficial for women with breast cancer [4, 5], and reduced symptom distress is a crucial outcome of successful psychosocial interventions [6]. Symptom management requires that women understand appropriate management strategies and have appropriate levels of self-efficacy and social support to apply such strategies [7].

Evidence suggests that Chinese women with breast cancer receive inadequate support from health care professionals [8]. The increasing number of women with breast cancer [1], the insufficient financial commitment to health care from the government (5.5% of the GDP) [9, 10], and the shortage of oncology specialists [9] pose challenges to the feasibility of traditional face-to-face interventions. Internet-based interactive programs (IIPs) that enable health care professionals and patients to interact with each other via the internet to transmit health information and to offer and accept support can provide an innovative and easily accessible approach that can reach large groups of patients [11, 12].

Although preliminary evidence suggests that IIPs have had a positive impact in facilitating symptom management among women with breast cancer in Norway and the United States [6, 13], there is a worldwide paucity of rigorous trials that have evaluated the effectiveness of internet-based interventions for women with breast cancer [14]. In mainland China, there has been only limited investigation of the effectiveness of IIPs among Chinese women with breast cancer. Two such studies, published in Chinese, reported that IIPs improved symptom distress and self-efficacy [15] and decreased depression among women with breast cancer [16]. These two studies on IIPs in the Chinese population showed that the internet could be a useful tool for educating women about breast cancer. However, these two studies were not performed using randomised controlled trials (RCT). To the best of our knowledge, no RCTs have been conducted in Mainland China that evaluate the effects of an IIP for women with breast cancer undergoing chemotherapy.

In 2015, 50.3% of China’s population frequently used the internet [17], and 88.9% of these people access the internet by mobile devices [18]. With more women turning to mobile phone to search for information, mobile Applications (Apps) could provide a promising platform to apply IIP for women with breast cancer. However, a review of smartphone breast Apps reported the lack of evidence base and medical professional involvement in their development [19]. To improve women’s confidence in the use of Apps and further promote the implementation in health service, Mobasheri et al. [19] recommended that a robust framework, full authorship disclosure, and high quality clinical trials are needed to develop and test the effectiveness of Apps for women with breast cancer.

### The breast cancer e-support program (BCS)

The Breast Cancer e-Support program (BCS) is a mobile IIP application (App) for Chinese women with breast cancer who are undergoing chemotherapy. The BCS was developed using the theoretical framework [20], which incorporate Bandura’s self-efficacy theory [21] and the social exchange theory [22]. Appropriate levels of self-efficacy and social support are essential components of interventions to improve patients’ symptom management [23]. The BCS aims to enhance women’s self-efficacy and social support to promote their ability to manage the symptoms associated with breast cancer diagnosis and chemotherapy, thus improving their QoL and psychological well-being.

Self-efficacy, an individual’s perception of her ability to act effectively in a given situation, plays a crucial role in influencing a woman’s ability to manage her symptoms [21]. Self-efficacy comprises four main factors: direct mastery experiences, vicarious experiences, verbal persuasion and arousal state [21]. Direct mastery experiences involve previous personal accomplishments and successes. Vicarious experiences are gained by watching others achieve success in similar situations. Verbal persuasion comes from feedback and verbal cues from others. Finally, arousal states are defined as a person’s physiological state and their perception of that state.

Social support is defined as a combination of structural support and functional support [22]. Structural support consists of formal support from health care professionals and informal support from significant others. Functional support consists of exchange activities that take place among individuals, including emotional, instrumental, informational, and appraisal support. Access to a variety of types of functional support from different care providers, both health care professionals and significant others, is important for coping with stress [22].

The BCS program is a multi-component intervention that includes a Learning forum, a Discussion forum, an Ask-the-Expert forum, and a Personal Stories forum. Four factors from the self-efficacy theory [21] and the functional and structural social support concepts from the social exchange theory [22] are incorporated into the BCS program. Regarding the self-efficacy theory, mastery experiences include the provision of symptom management knowledge in the Learning forum; vicarious experiences involve reading others’ personal stories in the Personal Stories forum and sharing experiences in the Discussion forum; verbal persuasion comes from feedback and verbal cues from peers and health care professionals in the Discussion forum and Ask-the-Expert forum; and the learning materials and sharing of experiences may modify women’s perceptions of their expected arousal states. In terms of social exchange theory, the Discussion and Ask-the-Expert forums are designed to build structural social networks and provide multiple types of functional support from peers and health care professionals. Figure 1 illustrates the theoretical framework of the BCS.

**Fig. 1 Fig1:**
[figure not shown]
Theoretical framework of the Breast Cancer e-Support Program - adapted from Shorey et al. [21]

### Objectives

The objective of this RCT is to evaluate the effectiveness of the BCS program for Chinese women with breast cancer undergoing chemotherapy in terms of enhancing the women’s self-efficacy, social support and QoL, and reducing their symptom distress, anxiety and depression.

We hypothesise that compared with the control group at baseline, post-test 1 and post-test 2, the women with breast cancer who are undergoing chemotherapy in the experimental group will have the following significant differences:

1. Improved self-efficacy, social support and QoL;

2. Reduced symptom distress, anxiety and depression; and

3. Greater satisfaction with the health care received during chemotherapy.

### Trial design

A single-blinded, multicentre, randomised, controlled, parallel-group pre-test and repeated post-test superiority design will be used to investigate the effect of the BCS program for women with breast cancer who are undergoing chemotherapy.

## Methods

The study follows the SPIRIT 2013 Statement and the guidelines for the Standard Protocol of Clinical Trials [24, 25]. The study received ethic approval from the University of Newcastle in Australia and the two participating hospitals in P. R. China. The registration number with the Australian New Zealand Clinical Trials Registry is ACTRN12616000639426.

### Study setting

This study will be conducted in two university affiliated tertiary public hospitals in the People’s Republic of China. At each participating hospital, an average of 40 women with breast cancer per month receive chemotherapy; approximately 15 of these women have access to the internet. The usual treatment for women with breast cancer at these two participating hospital consists of four cycles of chemotherapy, with each cycle lasting 21 days.

### Eligibility criteria

Participants will be recruited on the day they commence chemotherapy. The inclusion criteria will be: (1) at least 18 years of age; (2) diagnosed with breast cancer within the past 3–8 weeks; (3) treated with chemotherapy at the study sites; (4) able to access the internet with a mobile phone; (5) cognitively and physically capable of participating and completing self-report questionnaires; (6) contactable via telephone or email for follow up; and (7) able to speak and read Mandarin. The exclusion criteria for women will be: (1) having a concurrent major physical illness and (2) having a chronic mental health problem.

### Intervention

#### BCS program

A research team at the School of Nursing and Midwifery at the University of Newcastle, Australia, developed the intervention, with technical assistance from the Suncco Internet Company in the People’s Republic of China. The BCS program is supported by the National Natural Science Foundation of China (71503219).

The Breast Cancer e-Support (BCS) program has a fixed structure that covers four cycles of chemotherapy, which last approximately 12 weeks. Data from previous studies suggest that IIPs provide the greatest benefits to women that have recently been diagnosed with breast cancer and are in the early stages of treatment [26], and that an 8-week online intervention is enough to produce changes in psychological outcomes [27]. Thus, a 12-week intervention is considered sufficient to test the effectiveness of the BCS. A pamphlet has been developed to provide guidance for downloading the BCS program from the website http://breastesupport.xmu.edu.cn/, and navigating the various sites within the BCS. It is up to the women to decide how often they access the BCS and how long they use the intervention.

The BCS has four modules: 1) a Learning forum; 2) a Discussion forum; 3) an Ask-the-Expert forum; and 4) a Personal Stories forum. These four modules are visually recognisable on the homepage of the BCS (see Fig. 2). The Learning forum provides 15 topics on symptoms management, including 1) nausea and vomiting management; 2) improving diet by making healthier food choices; 3) exercise and recovery; 4) how to deal with hand-foot syndrome; 5) how to deal with upper limber lymphoedema; 6) infection prevention and management; 7) fatigue management; 8) how to deal with depression and anxiety; 9) alopecia management; 10) oral mucositis management; 11) constipation management; 12) sleep management; 13) diarrhoea management; 14) how to deal with body changes; 15) bleeding and anaemia management. To create the 15 topics, detailed discussions with multidisciplinary Chinese oncology professionals were carried out. The Learning forum also provides basic information about breast cancer symptoms, diagnosis, stages, treatment options and community support service.

**Fig. 2 Fig2:**
[figure not shown]
Screenshots of the BCS program home page and the four modules

The Discussion forum and the Ask-the-Expert forum provide opportunities for social networking. In the Discussion forum, women will be invited to discuss symptom management topics and to share information and experience. In the Ask-the-Expert forum, health care professionals (a doctor and a senior nurse) will respond to health-related questions posed by individuals within 24 h. Only the individual that posed the question and the health care professionals will have access to the question and to the response. In the Personal stories forum, five recorded interviews with women who completed chemotherapy after breast cancer diagnosis and surgery will be available. Women with different stages of breast cancer, different ages, and different socio-economic statuses will be interviewed and recorded to provide role models for women with different needs. The moderator, an experienced health care professional, will moderate the online forum by reading all messages daily, facilitating online discussions, providing expert information when requested, and intervening appropriately if the messages posted are inappropriate or hostile.

#### Privacy

A member of the research team will help the women in the intervention group to register with the BCS program. The women will be initially assigned their mobile phone number as the user name; however, they can change their user names later by themselves. The women will submit their applications to the BCS program. Once the researcher approves applications through the App background management system, they women will set their own passwords. The user name will expire 12 weeks after activation. The participants will be informed that the researcher can access their profile.

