#### Support

The researcher will offer personal training (averaging 30 min) to the experimental group to help its members download and install the App onto their mobile phones, demonstrate the usage of each module of the BCS, and help the women write an introductory message in the Discussion forum and ask a question in the Ask-the-Expert forum.

Technical assistance will be available via email or telephone from 8:00 am to 5:00 pm from Monday to Friday. At other times, users can email a technical assistant or leave a message on voicemail. A technical assistant will check emails and voicemail messages five days a week and respond to the women as soon as possible.

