### Ethics, consent and permissions

The ethics approval for this study has been obtained from the Human Research Ethics Officer at the University and the participating hospitals. This study will adhere to ethical standards for the whole procedure. Women will not be deprived of any treatment and routine care, and there is no potential rick or harm by participating in this program. Women will be assured that participation in this study is voluntary and they can withdraw from the study at any point of time without any effect on their treatment. The consent form will be obtained and all data will be kept confidential and anonymous.

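### Intervention-group women start with their mobile phone number as user name and are coached to post in a shared forum, with no step that replaces it first and no statement of whether peers see it

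*Protocol article*

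**What the plan says.** All of this is in the protocol article.

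- **Privacy (under Intervention).** Accounts are for the intervention group: "A member of the research team will help the women in the intervention group to register with the BCS program". The starting name is set as follows: "The women will be initially assigned their mobile phone number as the user name; however, they can change their user names later by themselves". The researcher approves each application, the woman then sets a password, and she is told that the researcher can open her profile.
- **Support.** The researcher gives personal training, averaging 30 minutes, in which staff "help the women write an introductory message in the Discussion forum and ask a question in the Ask-the-Expert forum".
- **Intervention, text following Fig. 2.** On the first forum: "In the Discussion forum, women will be invited to discuss symptom management topics and to share information and experience". On the Ask-the-Expert forum: "Only the individual that posed the question and the health care professionals will have access to the question and to the response". No such restriction is stated for the Discussion forum. The moderator reads all messages daily, and the duties include "intervening appropriately if the messages posted are inappropriate or hostile".
- **Internet usage data for the BCS.** Login frequency, login duration and activity in each module are recorded and evaluated.
- **Ethics, consent and permissions.** The section states that "all data will be kept confidential and anonymous", and it denies, without qualification, that taking part carries any potential risk or harm.

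**The concern.** A mobile phone number identifies its owner directly. The App is for women with breast cancer undergoing chemotherapy, so an identifier shown in its forum is tied to that diagnosis. The protocol makes the number the default and leaves any change to the woman at some later time, yet the first forum message is prompted by trial staff. If the name is shown with posts, disclosure would follow from doing what the training asks, and a number once seen by others cannot be recalled.

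The ethics section adds a second problem. Its assurances on anonymity and on the absence of risk are absolute, while other sections describe named accounts, tracked use and a forum hazard that needs moderation.

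**Working it through.** No formula applies; the check sets the sections side by side.

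**1. Whom the rule covers.** Registration is described for the intervention group, and the Comparison section states that controls have no access. Randomisation draws 27 experimental slips at each of two hospitals, so 27 × 2 = 54 women, which agrees with the 54 per group under Sample size. This is the number to whom the default applies. It is not a count of women exposed.

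**2. What the name is at the first post.** Privacy gives the phone number as the initial name and places any change later, in the woman's hands. Support lists what the training contains: download, installation, demonstration of the modules, the introductory message and a question to the expert. Neither section includes a step that replaces the name. The default could therefore still be in force at the coached post, although the article does not say so.

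**3. Who reads the post.** The Discussion forum exists for women to exchange experience with each other. Restricted access is stated only for the Ask-the-Expert forum. The introductory message is therefore read by peers.

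**4. Whether peers see the user name.** Not stated. Setting the rule under the Privacy heading, with the reminder that the name can be changed, suggests that it matters beyond log-in. It is also introduced alongside applications, approval and passwords, which fits a log-in credential. The Fig. 2 screenshots are not available. The exposure is therefore conditional on display.

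**5. Anonymity against the procedures.** Accounts begin under a phone number, the researcher can open profiles, and logins and module activity are recorded for evaluation. Women must also be contactable for follow-up (Eligibility criteria) and are measured at three times (Recruitment). Such data can be confidential and coded; they are not anonymous. This holds whether or not peers see the user name.

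**6. Absence of risk against the procedures.** The moderator's duties include acting on inappropriate or hostile messages. The protocol thus foresees a hazard that the ethics section says does not exist. This too is independent of how names are displayed.

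**The case against.** The strongest reply is that the key premise is missing: no section says user names are shown with posts, and the name may serve for log-in only. That stands, and the disclosure point must remain conditional.

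It can also be said that registration and training are described separately, so a woman might have changed her name before posting. That is possible, but no section provides for it.

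Third, the confidentiality statement can be read as covering research data rather than forum names, and the consent form is not shown. This removes any claim that confidentiality is plainly breached or that a promise in the consent form is broken. It does not rescue the word *anonymous*, because usage data are themselves listed among the outcomes.

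Fourth, the audience is limited to approved accounts held by fellow participants, and a health care professional moderates daily. Both are true. They limit the risk without supporting a statement that there is none.

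Finally, an article condenses its protocol. Here, however, the article itself states the default and the two assurances, and the point is about those statements.

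A reader might go further and infer that all 54 women will have their numbers disclosed, or that women who feel identifiable will post less and so weaken the intervention. The first needs the unstated display rule. The second has no support in the document.

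**Conclusion.** The point holds as a potential disclosure that the protocol leaves unaddressed. The default user name is a direct identifier, staff coach a post in a shared forum, and nothing replaces the name first. Actual disclosure to peers rests on two assumptions: that user names are displayed with posts, and that the default is unchanged at the first post. Neither is stated, so no number exposed can be given.

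Two inconsistencies need no such assumption. Anonymity does not fit phone-number accounts, researcher-accessible profiles and tracked logins. The denial of any risk conflicts with the hostile messages the protocol foresees. On their own these would be minor wording points; what justifies a change is that a safer default costs almost nothing.

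There is no effect on sample size, power or analysis.

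**What to change.** 1. **Privacy section.** At registration, assign a study code or a pseudonym chosen by the woman, before the introductory message is written. Keep the phone number only in the background management system. State whether user names are visible to other participants.
2. **Ethics section.** Describe the data as coded and confidential instead of anonymous. Replace the denial of any risk with a sentence that names the forum privacy risk and the possibility of hostile messages, and refers to the moderation already planned. Reconcile this with the Privacy section, the forum description and the usage-data section.

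The cost is a changed registration default, a link between code and phone number to maintain securely, and a few sentences of text. No extra staff or visits are needed. If user names prove to be hidden from peers, saying so closes the disclosure question, and the ethics text still needs correction.
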